### Intervention studies to prevent catheter-related infections

Previous research suggests that multiple and well-organized interventions could reduce the number of HAIs. In a pilot study in our university hospital in the Netherlands 89.2% of the initial indications for urinary catheter use were appropriate. However, after 2–3 days the initial indication was mostly no longer present, resulting into an inappropriate indication, but not to a removal of the catheter. After education and daily assessment of the indication of urinary catheters, the duration of catheterization reduced from 1009 to 672 days in 149 patients (pre-intervention *n* = 74, post-intervention *n* = 75), and the number of catheter-associated urinary tract infections (CAUTI) decreased from 4 to 0 infections per 1000 catheter days (*p* = 0.04). Thereby the median length of hospital stay reduced from 13 to 9 days [20]. Very recently, a national program (dissemination of information to sponsor organizations and hospitals, data collection, and guidance on key technical and socioadaptive factors) in 603 US hospitals reduced CAUTI rates by 22% in non-ICUs [21].

Only a few studies evaluated the effect of interventions to improve the appropriate use of PIVCs. In 1994 a quality improvement project in the internal medicine wards of Minnesota reduced inappropriate use of PIVCs by 63% (43% vs 27%) [22]. Education and feedback to improve PIVC care significantly reduced the PIVC-associated bloodstream infections from 2.2 to 0.44 per 10.000 patients days in 10 non-ICUs [23]. Furthermore, in a general hospital in Spain the use of unnecessary peripheral and central venous lines decreased from 22.9 to 7.1% after a 1-year training program [24].

A multifaceted ‘bundle’ approach (education, hospital protocol, national program, and checklist intervention) to control CVC-associated bloodstream infection in an internal medicine department in Spain showed a decrease of 63.1% (14.1 to 5.2 per 1000 catheter days) [25].

Prevention of HAIs is an important part of the todays medical practice. However, the risks of the use of urinary catheters and mainly PIVCs are widely underestimated, and in the Netherlands no nationwide program to reduce the catheter-related infections is present.

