Arterial or venous infection (VASC)	It must meet at least one of the following criteria: 1. Patient has organisms from extracted arteries or veins identified by a culture or non-culture based microbiologic testing method which is performed for purposes of clinical diagnosis or treatment. 2. Patient has evidence of arterial or venous infection on gross anatomic or histopathologic exam. 3. Patient has at least one of the following signs or symptoms: fever (>38.0 °C), pain, erythema, or heat at involved vascular site AND more than 15 colonies cultured from intravascular cannula tip using semiquantitative culture method. 4. Patient has purulent drainage at involved vascular site.
Urinary tract infection (UTI)	Patient has at least one of the following signs or symptoms: fever >38.0 °C, suprapubic tenderness, costovertebral angle pain or tenderness, urinary urgency, urinary frequency, dysuria^a^ AND urine culture with no more than two species of organisms identified, at least one of which is a bacterium of ≥10^5^ CFU/ml
Indwelling catheter (Foley catheter)	A drainage tube that is inserted into the urinary bladder through the urethra, is left in place, and is connected to a drainage bag.
Catheter-associated UTI (CAUTI)	A UTI where an indwelling urinary catheter was in place for >2 calendar days on the date of event, with day of device placement being Day 1, AND an indwelling urinary catheter was in place on the date of event or the day before

^a^An indwelling urinary catheter in place could cause patient complaints of frequency, urgency, or dysuria, and therefore these cannot be used as symptoms when catheter is in place

**Table 3 Tab3:** Probable definition of catheter-related infections [31]

Catheter-related infection	Definition
Probable laboratory-confirmed bloodstream infection (LCBI)	Patient has at least one of the following signs or symptoms: fever >38.0 °C, chills, or hypotension AND organism(s) identified from (peripheral) blood or catheter segment is not related to an infection at another site AND defervescence within 48 h of catheter removal or initiation of appropriate antibiotic therapy
Probable central line-associated BSI (CLABSI)	A probable LCBI where the central line was in place for >2 calendar days on the date of event, with day of device placement being Day 1, AND the central line was also in place on the date of event or the day before

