Phlebitis	Local pain, warmth, tenderness, erythema, and a palpable cord along the vein OR by positive sonographic examination in conjunction with erythema and edema of the extremity
Probable urinary tract infection (UTI)	Patient has at least two of the following signs or symptoms: fever >38.0 °C, suprapubic tenderness, costovertebral angle pain or tenderness, urinary urgency, urinary frequency, dysuria^a^ AND positive nitrite or leukocyte esterase dipstick test OR pyuria (>10 leukocytes/mm^3^) OR organism(s) seen in gram straining in not centrifuged urine OR two sequential urine culture (≥10^2^ CFU/ml) with the same uropathogens (gram negative bacteria or S. saprophyticus) OR urine culture with one species of organism identified (≤10^5^ CFU/ml) in a patient treated with appropriate antibiotic therapy OR the diagnose ‘urinary tract infection’ by doctor OR doctor starts appropriate antibiotic therapy
Probable catheter-associated UTI (CAUTI)	A probable UTI where an indwelling urinary catheter was in place on the date of event or the 7 days before

^a^An indwelling urinary catheter in place could cause patient complaints of frequency, urgency, or dysuria, and therefore these cannot be used as symptoms when catheter is in place

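### Probable CAUTI is scored on three symptoms with the catheter in and on six for 7 days after removal, so earlier removal can attenuate a true reduction

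*Protocol article*

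**What the plan says.** All of the rules are in the protocol article, under Definition of catheter-related infections.

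- **Probable UTI (Table 3).** The entry requires "Patient has at least two of the following signs or symptoms", from the list "fever >38.0 °C, suprapubic tenderness, costovertebral angle pain or tenderness, urinary urgency, urinary frequency, dysuria", together with one of several laboratory, diagnostic or treatment items.
- **Footnote a to Table 3.** Frequency, urgency and dysuria may be caused by the catheter itself, "and therefore these cannot be used as symptoms when catheter is in place".
- **Probable CAUTI (Table 3).** "A probable UTI where an indwelling urinary catheter was in place on the date of event or the 7 days before". No minimum dwell time is set.
- **CAUTI (Table 2).** More than 2 calendar days in place, and "an indwelling urinary catheter was in place on the date of event or the day before".

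The same section plans to use both the Table 2 and the Table 3 definitions. The Assessments section, which describes what is collected after discharge, refers to Table 3 only. Catheter-related infections are a secondary endpoint (Primary and secondary endpoints), and catheter-related complications enter the Economic evaluation. The strategy recommends removing catheters that have no valid indication or whose indication has expired (De-implementation strategy), and it expects fewer catheter days (Objectives).

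**The concern.** The date of catheter removal switches the scoring rule from three eligible symptoms to six. That date is also what the intervention is meant to change. If removal comes earlier after the intervention, more of each patient's attribution window lies under the rule that is easier to satisfy. Ascertainment of probable CAUTI then differs between the two periods for a reason unrelated to infection, and the difference works against the strategy.

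At stake is a secondary endpoint, and through it one input to the economic evaluation. The primary endpoint concerns indications and is not touched.

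**Working it through.** The article gives no figure for this, so there is none to reproduce. The check has four steps.

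**1. Symptom rule.** With the catheter in, 3 symptoms are eligible and C(3,2) = 3 pairs satisfy the two-symptom criterion. After removal, 6 are eligible and C(6,2) = 15 pairs do. To turn this into a detection ratio, assume independent symptoms with equal probability p. The ratio is P(at least 2 of 6) / P(at least 2 of 3):

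| p (assumed) | 3 eligible | 6 eligible | ratio |
|---|---|---|---|
| 0.02 | 0.00118 | 0.00569 | 4.8 |
| 0.05 | 0.00725 | 0.03277 | 4.5 |
| 0.10 | 0.02800 | 0.11427 | 4.1 |
| 0.20 | 0.10400 | 0.34464 | 3.3 |

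The article gives no symptom frequencies. A fourfold ratio is used below as an assumption within this range.

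**2. Dwell time.** The pilot described under Intervention studies to prevent catheter-related infections reports that "the duration of catheterization reduced from 1009 to 672 days in 149 patients", with 74 patients before and 75 after. Taking these as total catheter days, mean dwell is 1009/74 = 13.635 days before and 672/75 = 8.96 days after.

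**3. Share of the window under the looser rule**, if all 7 post-removal days are observed:

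- before: 7/(13.635 + 7) = 7/20.635 = 33.9%
- after: 7/(8.96 + 7) = 7/15.96 = 43.9%

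**4. Expected scored events per patient**, in units of a constant daily rate, with k the relative detection after removal:

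post/pre ratio = (8.96 + 7k) / (13.635 + 7k)

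- k = 1 (same rule in both states): 15.96/20.635 = 0.77
- k = 2: 22.96/27.635 = 0.83
- k = 4: 36.96/41.635 = 0.89
- k = 5: 43.96/48.635 = 0.90

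At k = 4 a 23% reduction would show as 11%. The ratio stays below 1 for every k, so on these inputs the effect is attenuated and not reversed.

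**Dependence on stay after removal.** Replace the fixed 7 days by min(7, discharge day − removal day):

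| Removal day, before to after | Discharge day, before to after | k = 1 | k = 4 |
|---|---|---|---|
| 10 to 6 | 20 to 20 | 13/17 = 0.76 | 34/38 = 0.89 |
| 11 to 7 | 13 to 9 | 9/13 = 0.69 | 15/19 = 0.79 |
| 13 to 9 | 13 to 9 (removal at discharge) | 9/13 = 0.69 | 9/13 = 0.69 |

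In the last row there is no post-removal time and no bias.

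**The case against.** **Reversal.** A reader might infer that early removal will be made to look harmful. The document does not support that. With a full window the per-patient ratio is below 1 whatever k is. Reversal needs a special pattern, such as discharge fixed on day 13 while removal moves from day 13 to day 9: the ratio is then 13/13 = 1.00 at k = 1 and 25/13 = 1.92 at k = 4. The pilot does not suggest that pattern, because its median stay also fell, from 13 to 9 days.

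**Rate per catheter day.** A reader might also calculate that such a rate is inflated by 18% (1.781/1.513, equal daily hazard) or 11% (1.391/1.257, half the hazard after removal). Those figures contain no symptom effect. They arise only from counting 7 extra days in the numerator and not in the denominator, and the article fixes no denominator for infections.

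**Full 7-day window.** Nothing in the article shows that seven days after removal are observed for everyone. Outcomes come from medical and nursing records, where symptoms at home may not appear. The 34% and 44% shares are therefore near an upper bound.

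**A stricter definition is planned.** Table 2 CAUTI limits the post-removal period to one day. This stands, although the Assessments section does not carry it through.

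**Footnote a has a clinical reason.** Lower urinary symptoms are weak evidence of infection with a catheter in place and better evidence once it is out. Restricting the main definition to three symptoms could miss genuine post-removal infections, more of them after the intervention, and so favour the strategy. This stands, and it is why the definition itself should be kept.

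**Wording of probable UTI.** The entry is an unbracketed chain of AND and OR. Read literally, a doctor's diagnosis or a treatment start might suffice without symptoms, which would weaken the asymmetry. Two symptoms plus any one listed item is the more natural reading and is the one used here.

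**Conclusion.** The point holds as a difference in ascertainment tied to the intervention. Three symptoms count in place and six after removal, the looser rule runs for up to 7 days, and earlier removal can raise its share of the window. The expected direction is attenuation of a true reduction in probable CAUTI.

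The size cannot be derived from the document. The move from 0.77 to 0.89 is an illustration that rests on pilot dwell times, a constant daily rate, a fully observed 7-day window and an assumed fourfold detection. The effect is smaller if stay after removal is short, and absent if catheters remain until discharge in both periods. It concerns one component of a secondary endpoint and what the economic evaluation takes from it.

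**What to change.** Keep the Table 3 definition and change the reporting of the before–after comparison:

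1. Report probable CAUTI in two lines: events with the catheter in place and events after removal.
2. Add a sensitivity comparison that applies fever, suprapubic tenderness and costovertebral angle pain or tenderness, the symptoms usable in both states, throughout the window.
3. Show Table 2 CAUTI alongside, and bring the Assessments section into line with the definitions section, so that both sets are collected.
4. If a rate is reported, use catheter days plus observed post-removal days, up to 7, as the denominator. This corrects the denominator only; items 1 and 2 address the symptom rule.

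The cost is a few sentences and slightly more analysis. Symptoms and the timing of removal are already needed to apply Table 3, and catheter days and length of stay are already collected. The small downside is that the sensitivity comparison is less sensitive to post-removal infections with lower urinary symptoms only, so it should be read beside the main definition and not in its place.

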### Patient selection

We will include all patient (≥18 years old) admitted to internal medicine and subspecialties (gastroenterology & hepatology, geriatrics, pulmonology and rheumatology) and all nonsurgical patients admitted to acute medical units, who receive urinary and/or (peripheral and/or central) intravenous catheter. Patients admitted for elective short stay, terminally ill patients and patients who had all catheters prior to admission will be excluded (Fig. 2).

**Fig. 2 Fig2:**
[figure not shown]
Flowchart of patient inclusion

### Primary and secondary endpoints

The primary endpoint is the percentage of patients with an inappropriate indication for urinary and intravenous catheter on the days of data collection. Secondary endpoints are catheter-related infections and other complications, catheter reinsertion rate, use of antibiotics, length of hospital stay (and ICU) in days, in hospital mortality, and costs of the de-implementation strategy and the main healthcare costs.

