**Methods:**

In a multicenter, prospective interrupted time series analysis, several interventions to avoid inappropriate use of catheters will be conducted in seven hospitals in the Netherlands. Firstly, we will define a list of appropriate indications for urinary and (peripheral and central) intravenous catheters, which will restrict the use of catheters and urge catheter removal when the indication is no longer appropriate. Secondly, after the baseline measurements, the intervention will take place, which consists of a kick-off meeting, including a competitive feedback report of the baseline measurements, and education of healthcare workers and patients. Additional strategies based on the baseline data and local conditions are optional. The primary endpoint is the percentage of catheters with an inappropriate indication on the day of data collection before and after the de-implementation strategy. Secondary endpoints are catheter-related infections or other complications, catheter re-insertion rate, length of hospital (and ICU) stay and mortality. In addition, the cost-effectiveness of the de-implementation strategy will be calculated.

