### Assessments

The presence and indications for the catheter use will be extracted from the medical records in combination with observations of the admitted patients. During the day of measurement the indication of the urinary and/or intravenous catheter and some patient variables will be collected. If there is an unclear indication of a catheter, the investigator will contact one of the healthcare workers (HCWs) to verify this information.

After discharge, the occurrence of catheter-related infections (see Table 3 for definitions) [31], with diagnostics and treatment, or other catheter-related complications (measured in registry and by investigator), the number of catheter days, reinsertion rate, use of alternatives for an indwelling urinary catheter (continence garments, condom catheters, intermittent straight catheterization), reason for admission, Charlson comorbidity index [32], duration of hospital (and ICU) stay, readmission within 30 days after discharge, and mortality (in hospital or within 30 days after discharge) will be collected from (electronic) medical- and nursing records. Furthermore, the nurse-to-patient ratios and the clinical work experience of residents will be collected.

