### Economic evaluation

The main question for the economic evaluation is if the benefits of a reduction in inappropriate use of catheters, which probably lead to a reduction in catheter-related infections, length of stay and associated costs, outweighed the costs associated with this de-implementation strategy. For feasibility reasons, we will use length of stay on general and ICU wards, readmission within 30 days of discharge, catheter-related complications, representing the main features of the healthcare system, and productivity costs for societal perspective. We will estimate the unit costs for healthcare service based on the prices in the Dutch guideline on healthcare costs [36]. We will divide the de-implementation costs in non-recurrent and recurrent costs. The non-recurrent costs are study-related, such as the costs of development of the de-implementation strategy, material costs, and costs of evaluation of the de-implementation. Recurrent costs are the costs to implement the de-implementation strategy. The primary analysis is a cost-effectiveness analysis, in which the difference in costs of the de-implementation and outcomes between the baseline and intervention group will be estimate using incremental cost-effectiveness ratios (ICERs). The cost-benefit analysis will be reported as the ratio of de-implementation costs to reduction of healthcare costs (de-implementation costs < reduction healthcare costs). Statistical uncertainty will be evaluated in sensitivity analyses, such as unit costs, preference weights, estimates of effectiveness and discount rate. The result from the economic evaluation will be extrapolated to the national level using a budget impact analysis according to the principles of the report of the International Society for Pharmacoeconomics and Outcome Research Task Force [37], conducted from societal perspective and health insurance or national health service perspective.

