## Discussion

This study protocol describes the design, de-implementation strategy and evaluation of the ‘Reduce the inappropriate use of urinary and intravenous catheters’ (RICAT)-study. It could prevent the inappropriate use of urinary and intravenous catheters. If cost-effective it provides a tool for a nationwide approach to reduce catheter-related infections and healthcare costs.

A potential limitation of an interrupted time series design is the nonexistence of a control group. However, this quasi-experimental design is considered to be one of the most effective and powerful designs when randomization is not desirable or possible [34]. Another limitation is the inability to evaluate the impact of an individual intervention. In order to estimate the impact of a single de-implementation strategy there should be enough time between the different intervention periods, which is not possible in our study. Nevertheless, the interventions are well suitable for a broad de-implementation in other hospitals.

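### The secondary mortality endpoint stops counting at discharge, so the shorter stay that the strategy is expected to bring would by itself tend to lower it

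*Protocol article*

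**What the plan says.** The section on primary and secondary endpoints places "length of hospital stay (and ICU) in days, in hospital mortality" next to each other as secondary endpoints. The abstract's Methods paragraph names "length of hospital (and ICU) stay and mortality", with no time window for mortality. The Assessments section states that "mortality (in hospital or within 30 days after discharge) will be collected", so deaths after discharge are gathered, but no section gives them an endpoint role.

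Two places set the expectation about stay. The Economic evaluation section speaks of a reduction in inappropriate use, "which probably lead to a reduction in catheter-related infections, length of stay and associated costs". The review of earlier intervention studies reports that in the pilot at the investigators' own hospital (74 patients before, 75 after) "the median length of hospital stay reduced from 13 to 9 days".

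The comparison is before versus after. The Discussion concedes: "A potential limitation of an interrupted time series design is the nonexistence of a control group".

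**The concern.** For in-hospital mortality the time at risk is the stay itself. If the strategy shortens stay, patients after the intervention are watched for less time than patients before it, and a death that would have been counted in hospital happens at home, uncounted. The endpoint then falls even when nobody's risk of dying has changed.

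There is no concurrent control in which the same artefact would show. The planned adjustment for secular trend does not remove it either, because a stay shortened by the strategy is part of the intervention effect and not of the underlying trend. A reported fall in in-hospital deaths could be read as a survival benefit, or could offset and so hide a real increase.

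**Working it through.** The protocol gives no mortality rate, hazard or power for mortality, so there is no figure of its own to reproduce. What follows is an illustration.

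**Inputs.** Stay L of 13 days before and 9 days after, taken from the pilot medians. Daily death hazard h identical in both periods, so there is no true effect; h is an assumption, varied from 0.001 to 0.010 per day.

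**1. Fixed stay, constant hazard, clock from admission.** In-hospital risk is 1 − exp(−hL). Counting to 30 days after discharge replaces L by L + 30, that is 43 and 39 days.

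| h per day | In hospital, 13 vs 9 days | Ratio | To 30 days after discharge | Ratio |
|---|---|---|---|---|
| 0.001 | 1.29% vs 0.90% | 0.69 | 4.21% vs 3.82% | 0.91 |
| 0.004 | 5.07% vs 3.54% | 0.70 | 15.80% vs 14.44% | 0.91 |
| 0.010 | 12.19% vs 8.61% | 0.71 | 34.95% vs 32.29% | 0.92 |

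**2. Exponential stay with the same medians, death competing with discharge.** In-hospital risk is p = h / (h + ln 2 / median). The ratio is 0.70 to 0.73 over the same range of h. To 30 days after discharge the risk is p + (1 − p)(1 − exp(−30h)), and the ratio is 0.89 to 0.92.

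**3. Clock from the measurement day.** Patients are enrolled on a measurement day, not at admission. If that day falls evenly over a fixed stay, in-hospital risk is 1 − (1 − exp(−hL)) / (hL). At h = 0.005:
- L = 13: 1 − 0.06293 / 0.065 = 3.2%
- L = 9: 1 − 0.04400 / 0.045 = 2.2%
- ratio 0.70

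Counted from admission at the same h, the risks are 6.3% and 4.4%. The absolute risks halve and the ratio stays the same. To 30 days after discharge the ratio is about 0.95.

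**4. Hazard lower late in the stay.** Let the hazard after day 9 be a fraction g of h. The ratio is [1 − exp(−9h)] / [1 − exp(−h(9 + 4g))]. At h = 0.004:
- g = 0.50: ratio 0.82
- g = 0.25: ratio 0.90
- g = 0.10: ratio 0.96
- g = 0: ratio 1.00

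**5. Smaller reductions in stay.** With a fixed stay, constant h = 0.004 and a 13-day baseline, a stay shorter by 10% gives about 0.90 and by 20% about 0.80.

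**6. Window of fixed length.** Thirty days from the measurement day gives every patient the same time at risk. The risk is 1 − exp(−30h) in both periods under constant hazard, ratio 1.00. Because the measurement day precedes discharge, this window never runs past the 30 days after discharge for which deaths are collected.

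**The case against.** A reader might infer that the endpoint section and the Assessments section contradict each other. They do not. One lists endpoints and the other lists data, and collecting more than an endpoint uses is normal practice. The abstract's plain wording can be taken as shorthand. Nor does the protocol treat mortality as its main safety measure; it stands in a list with infections, other complications and reinsertion.

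The size is also open to challenge, and this stands. The stays of 13 and 9 days are medians from one hospital's urinary-catheter pilot, whereas this study covers seven hospitals and also patients with intravenous catheters. The protocol says only that a shorter stay is probable. A constant hazard carried past discharge is a strong assumption: at 1% per day it has about 35% of patients dead by 30 days after discharge. Days cut from the end of a stay belong to patients thought fit to leave, and since "terminally ill patients and patients who had all catheters prior to admission will be excluded", some late in-hospital deaths will not enter the data at all. A relative fall of about 30% is therefore not a forecast.

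It can also be said that results will be given as rate ratios, and that with patient-days in the denominator the constant-hazard model gives exactly 1.00. The Statistical analysis section, however, sets no patient-day denominator for mortality, so this does not settle the matter.

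Finally, a fixed window has its own weak point. The named sources are medical and nursing records, with no separate source for deaths outside hospital. If such deaths are missed more often, earlier discharge could bring part of the artefact back.

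**Conclusion.** The concern holds in direction. In-hospital mortality has an observation window that the protocol expects the strategy to shorten, in a design without a concurrent control, so it is biased towards fewer deaths after the intervention. This needs only that stay shortens and that some deaths fall in the days removed; the bias vanishes only if none do.

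Its size cannot be derived from the document. With the pilot's stays, the ratio under no true effect is about 0.70 for a constant hazard and 0.82 to 0.96 if the hazard after day 9 is 50% to 10% of its earlier level. Hazards and stays are assumptions in every case. Moving to 30 days after discharge would lessen the artefact (ratio about 0.9 to 0.95 under constant hazard) but not remove it, since that window still contains the stay.

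Mortality is a secondary endpoint, and the primary endpoint is untouched. The change is still worth making, because it is small and prevents a misreading.

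**What to change.** In the section on primary and secondary endpoints, define the mortality endpoint as death within 30 days of the patient's first measurement day of the admission. Naming the first such day matters because measurements recur every 14 days and a long-stay patient can have several. Report in-hospital mortality beside it as descriptive, and use the same wording in the abstract.

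Add the date of death to the data collected. The Assessments section plans to record deaths over a window that already covers the new endpoint, but does not say that their dates are kept. Report the completeness of vital status after discharge separately for the periods before and after the intervention.

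The cost is one reworded endpoint, one extra data item and a completeness table. The small downside is that deaths after discharge may be less fully captured from hospital records than deaths in hospital.
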